### Participants: inclusion and exclusion criteria

The participants will be recruited from two districts (Haramaya and Kombolcha districts) based on pre-set eligibility criteria (pregnancy, gestational age (GA), ownership of a mobile phone and willingness to participate). The participant will be included in the trial if her GA is less than 16 weeks, she owns a mobile phone and has willingness to participate. The potential trial participants will be identified by the field worker-based enrollment criteria. For all eligible participants, the field workers will explain about study by reading the participant information sheets; if the study subjects are willing to participate, written informed voluntary consent will be obtained and baseline data collection will be made.

In this trial, study women who fulfill the enrollment criteria for the study but are critically ill at time of enrollment will be excluded from the study. Critically ill women are those pregnant mothers who unable to respond to interview questions because of illness. In addition, women with any systemic illness during this time will be excluded from the study. Any pregnant women with systemic illness need an special ANC follow- up, which is different from the recommended routine ANC follow -up and this set precondition without effect of treament for good adherence to maternal health care service use. Hence, any pregnant mother with known systemic illnesswill be excluded from this study.

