#### Screening and enrollment procedure

In this study, pregnancy, GA and ownership of mobile phone will be used as the main selection and enrollment criteria. Hence, in the selected kebeles, first, all the reproductive-age women with a history of amenorrhea for the last 28 days, who do not use any family planning, and who own a mobile phone will be screened for pregnancy through beta-human chorionic gonadotropin (HCG) urine test. Then, the mothers who are found to be positive for the HCG urine test will be given a unique identification number (ID No) and screened for GA through their last menstrual period (LMP) and/or portable ultrasound (U/S) scan result. Next, those women of less than 16 weeks of GA will be registered as illegible for the study. Finally, for each control and intervention group, 320 pregnant women who fulfill the enrollment criteria will be selected by a simple random-sampling method (computer-generated random table) [23]. They will be registered with their ID No and mobile phone number on a computer tablet.

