#### Phase II

This stage of data collection will be conducted after the eighth voice message or the fourth month of enrollment and the data collection will focus on maternal health condition, nutritional status and status of the voice messages which will be delivered to the intervention group, status of maternal health care service use among both intervention and control groups. During this period, data related to maternal health conditions will be collected through the same tools which will be used in phase I. In addition, data related to maternal health care services using status and voice message will be collected through a structured, interview-based questionnaire with confirmation of voice messages from their mobile phone.

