Published evidence supports the notion that the first ANC visit should be as early as possible in pregnancy, preferably in the first trimester (within the first 12 weeks of gestation) and in a normal pregnancy the protocol for pregnancy care recommends four ANC visits [24]. Hence, appointments for ANC follow-up will be adjusted based on GA with the first ANC visit preferably before 16 weeks of GA, otherwise at 16–24 weeks, the second ANC visit between 24–28 weeks, the third ANC visit between 28–32 weeks and the fourth ANC visit or last ANC visit between 32–40 weeks, preferably near to the EDD to ensure that the appropriate advice and care will be provided to prevent and manage problems such as multiple births (twins or more), post-maturity (which carries an increased risk of fetal death) and fetal mal-presentations. Therefore, based on the maternal enrollment framework criteria for this study, any mother with a GA of “*16 weeks-w*,” where “*w*” is any number of weeks less than 16, then the first voice message, which consists of reminders for the first ANC visit and information about advantage of this visit, will be sent. This voice message will be continued every 2 weeks until the end of the time frame for the first ANC visit which is 24 weeks of GA. Thus, a total of eight plus four voice messages will be sent as reminders for the first ANC visit and information about its advantages. Based on the time frame for the second ANC visit (24–28 weeks of GA), the 13th voice message from the initial message will be a reminder for the second ANC visit and information about its advantages. In this time frame, a maximum of two voice messages will be sent. The third stage of the voice message will be about reminders for the third ANC visit and its advantages. This stage of messaging will start from the 15th voice message and a total of two messages will be delivered. The last stage of voice messaging for ANC visit reminders and about its advantages will be started from the 17th voice message and this will consist of three parts (reminders for the fourth ANC visit, EDD and advantages of the fourth ANC and institutional delivery). A maximum number of voice messages from the date of enrollment and until the 42nd week of GA will be 21 voice messages. After the 21st voice message, the message will be changed to reminders for PNC follow-up and about its advantages. A total of three voice messages will be sent for PNC follow-up reminders and its advantages. Hence, an overall number of voice messages which will be sent for the intervention purpose will be 24. The content of all the messages will be first prepared in English and translated into the local language, “Afan Oromo,” and scripted to a female voice through a smart phone recording. Finally, these messages will be loaded on the mobile phone in voice message form to be sent regularly every 2 weeks at 7:00 a.m. to the intervention group:“Hello, this is voice message from a health center. How are you? We are sending this message to remind you about your first ANC visit. Maternal health care services are given free of any cost. This service will improve your health and your baby’s health. Please, come for your first antenatal care visit before 4 months (16 weeks), otherwise before 6 months (24 weeks) of your pregnancy. When you came for your first ANC service you will have a medical check-up, you will receive TT vaccine (medication that prevents tetanus from you and your baby), and you will also be given iron (element) and folic acid (medication which prevents anemia during pregnancy and promotes normal fetal growth). We are waiting for you to give free maternal health care services. If you have any problem please call to 09x……..”

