#### Control arm B

Participants in the control group will receive existing SOC which informs them about the advantages of maternal health care service use at HCs, informing them about the service which is given free of charge and giving appointments for regular follow-up. Unlike the intervention group, however, these participants will not be sent the voice message to remind for appointment and information about the advantage of maternal service use. With regards to the data collections, a house-to-house survey will be made among the households which will be identified with pregnant mothers who fulfill the inclusion and enrollment criteria. The three phases of the survey (I, II and III) will be made to collect data from the mothers who are in the trial. The survey will focus on maternal socio-demographic status, maternal health conditions, nutritional status, and health care service use and pregnancy outcome. The data collection tools will be the same for both trial arms (Trial arms A and B), except for mobile-phone-based voice message status.

For either intervention or control group if the study participants move from the study area before the study is completed, or withdraw from the study before the final data collection period, they will be registered as dropouts to follow-up.

Assuming that all mothers may give birth at different GAs their status of delivery will be tracked by fieldworkers and health professionals at selected HCs (Fig. 2).

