### Analysis plan: analysis of primary and secondary outcome

In this study, data will be collected at three phases. Phase I data collection will be done during enrollment time; phase II data collection will be conducted after 4 months of enrollment or after the eighth voice message; and end-line data collection or close-out time data collection (phase III data collection time) will be made after the 24th voice message. All the data will be checked for completeness at the time of data collection, coded and entered into Epi-Info-7 by using double-data entry method and they will be transported to STATA software Version 11 for analysis. Data cleaning will be done by the running of simple frequency distributions for internal consistency.

The report of this findings will be made according to the Consolidated Standards of Reporting Trials (CONSORT) standards for reporting RCTs. This is a behavioral intervention which is unlikely to cause adverse effects. Hence, the analysis will be done after the close-out time of the data collection. Intention-to-treat (ITT) principles will be used for primary outcome analysis; therefore, all the participants will be analyzed according to the arms they will be randomized to. During ITT analysis, the participants lost to follow-up, resulting in missing to maternal health care service use at close-out time of data collection, will be considered as non-health care service users.

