### Statistical method

For primary and secondary outcomes, Relative Risk with 95% confidence interval will be estimated. The association of dependent and independent variables will be checked by using the chi-square test. For count data, further analysis will be done by using multivariate count data logistic regressions or the Poisson Regression Model will be used to examine the effect of treatment on trial arms and Kaplan-Meier survival analysis will be used to compare maternal health care service use over time among treatment and control groups. Moreover, to adjust for both the clustering effect of the districts with their respective HCs and the participant-level intracluster correction, Generalized Estimating Equation (GEE) models will be used. All the analysis will be done by using STATA software.

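### Kaplan-Meier is named for service use over time with no time origin or rule for home birth; in its standard form it would overstate facility delivery and absorb differences in gestational age at entry

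*Protocol article*

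**What the plan says.** All from the protocol article.

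- **Statistical method.** The main effect measure is fixed first: "For primary and secondary outcomes, Relative Risk with 95% confidence interval will be estimated". The same section then adds that "Kaplan-Meier survival analysis will be used to compare maternal health care service use over time among treatment and control groups". It does not say which service is the event, what time zero is, or what happens to a woman who delivers at home or loses the pregnancy.
- **Who enters, and when.** Screening covers "all the reproductive-age women with a history of amenorrhea for the last 28 days", so entry can be as early as about 4 weeks. The upper limit is in the inclusion criteria: "The participant will be included in the trial if her GA is less than 16 weeks".
- **When services fall due.** Under Trial arm A, "appointments for ANC follow-up will be adjusted based on GA", with windows up to 16 weeks (otherwise 16–24), then 24–28, 28–32 and 32–40 weeks. Under Control arm B, the plan accepts that "all mothers may give birth at different GAs".
- **What is counted from enrolment.** Phase II takes place "after the eighth voice message or the fourth month of enrollment", and the analysis plan repeats that "phase II data collection will be conducted after 4 months of enrollment or after the eighth voice message".
- **Outcome definition.** Institutional delivery is birth at a health facility (Primary outcome measures). Under intention to treat, women lost to follow-up count as non-users.

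**The concern.** Two separate problems arise when Kaplan-Meier is applied to these outcomes in its usual way.

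1. **Competing events.** Kaplan-Meier knows only event or censored. A woman who has delivered at home can no longer deliver in a facility in that pregnancy. Censoring her treats her as someone who still could. Because every pregnancy ends, the curve is then pushed towards 100% in both arms, whatever the true facility share.
2. **Time scale.** ANC and birth are timed by gestational age. Time from enrolment to either is largely a measure of how far along the woman was when she joined. If one arm enrols later in pregnancy, its services appear to come sooner.

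The second problem carries extra weight in this design. Each arm is one district and one purposively chosen health centre, so randomisation cannot be relied on to balance gestational age at entry. The Discussion presents early initiation of care as what sets this trial apart, while the primary ANC outcome (at least one visit) ignores timing. A reader would therefore look to the time-based curves for evidence on that aim.

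**Working it through.** **The plan's own figure.** The sample size rests on two proportions, not on Kaplan-Meier. For 47% v 60%, two-sided 5%, 80% power and continuity correction, n = 246 per arm; 246 × 1.3 = 319.8, rounded up to 320. It reproduces and is not affected by this point.

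**Inputs from the protocol.** Facility shares 47% and 60% (Sample size determination); entry from about 4 to under 16 weeks.

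**Assumptions not in the protocol.** Entry age uniform over 4–16 weeks; gestational age at birth normal with mean 39.3 and SD 1.8, limited to 28–42 weeks; place of birth independent of its timing; no abortions or dropouts.

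**Formulas.** Let F(t) be the proportion who have given birth by time t, and p the facility share.

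- True proportion with a facility birth by t: p × F(t).
- Kaplan-Meier with home births censored: 1 − (1 − F(t))^p.

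**(a) Competing events, time from enrolment.** Simulation with 400,000 women per arm agrees with these formulas.

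| Weeks from enrolment | F(t) | 1−KM, 47% arm | 1−KM, 60% arm | True, 47% arm | True, 60% arm |
|---|---|---|---|---|---|
| 30 | 0.56 | 0.32 | 0.39 | 0.26 | 0.34 |
| 34 | 0.88 | 0.62 | 0.71 | 0.41 | 0.53 |
| 37 | 0.99 | 0.89 | 0.94 | 0.47 | 0.59 |

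At 37 weeks, with F = 0.991, the 47% arm gives 1 − 0.009^0.47 = 0.89, against 0.47 × 0.991 = 0.47. The difference between arms shrinks from about 13 points to 5. The shrinkage comes late: at 30 weeks the gap is about 7 points on either reckoning, although both levels are already too high. By the end of follow-up both curves reach about 1.0.

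Moving to gestational age alone does not cure this. With home births still censored, 1−KM at 41 weeks of gestation is 0.56 against a true 0.39, and 0.65 against a true 0.50.

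**(b) Time scale, no treatment effect.** Both arms have p = 0.47. One enters uniformly over 4–16 weeks (mean 10), the other over 8–16 (mean 12). At 30 weeks from enrolment, F = 0.563 and 0.813.

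- Time scale alone (correct cumulative incidence): 0.47 × 0.563 = 0.26 v 0.47 × 0.813 = 0.38, a 12-point artefact.
- With home births also censored: 1 − 0.437^0.47 = 0.32 v 1 − 0.187^0.47 = 0.54 (to within a point), a 22-point artefact.

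For first ANC visit, assume the same pattern in both arms (gestational age at first visit normal, mean 20, SD 4). An arm entering at 8–16 weeks then shows 48% with a visit within 8 weeks, against 19% for an arm entering at 4–12 weeks. This uses a larger, 4-week shift in mean entry age.

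**(c) After the change.** Cumulative incidence on the gestational-age scale ends at 0.47 and 0.60. Keeping home births in the risk set as event-free gives the same end values.

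**The case against.** The strongest reply is that the article commits to neither choice examined above. It gives Kaplan-Meier one clause, with no time zero, event or censoring rule, and such details are commonly left to an analysis plan that is not shown. That stands. A reader might infer that the curves as written are wrong; the text does not support this, because the plan could still use gestational age with delayed entry and keep home births in the risk set. Counting women lost to follow-up as non-users sits well with that second choice, and message content and ANC windows already follow gestational age.

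Other parts of the reply also stand:

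- The event is not said to be institutional delivery. For first ANC visit home birth matters little, and only the time scale counts.
- The article does not suggest any imbalance in entry age; the 2-week shift is an assumption. Nearly half of the 22-point null gap comes from assumed censoring, not from the time scale.
- A reader might infer that the primary result is at risk. It is not: the stated effect measure is the relative risk, with GEE for clustering.
- These curves are not the only place where timing enters. The per-protocol section classes women by whether visits fell within the recommended windows.

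What the reply does not remove is that the document names an estimator which, in ordinary use, does not estimate the proportion delivering in a facility. The objection is to the method chosen, which goes beyond a missing detail.

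**Conclusion.** The point holds in conditional form. Kaplan-Meier is planned without a time origin or a rule for home birth and pregnancy loss, and its standard form suits these outcomes badly. Under the stated assumptions it would show 89% v 94% facility delivery at 37 weeks from enrolment, where the true values are 47% v 59%. With no effect and a 2-week shift in mean entry age, it would show 26% v 38% at 30 weeks from the time scale alone, or 32% v 54% with censoring added. The direction of both biases follows from the structure of the outcomes; the sizes depend on the assumed distributions of entry and birth, and the second bias also on an imbalance that may not occur. The consequence is confined to a supplementary analysis, but one that bears on early initiation of care. It should be changed before analysis; it does not threaten the relative-risk results or the sample size.

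**What to change.** In Statistical method, replace Kaplan-Meier with cumulative incidence (Aalen-Johansen) on the gestational-age scale, with delayed entry at the gestational age of enrolment, and state the events:

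- **Facility birth:** home birth and abortion are competing events. Keeping those women in the risk set as event-free is equivalent for the final proportion.
- **First ANC visit:** end of pregnancy without ANC is the competing event.
- **PNC:** time runs from birth.

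Both parts are needed. Competing events alone leave the 26% v 38% artefact; the gestational-age scale alone leaves 56% against a true 39% at 41 weeks.

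The cost is analysis wording, with no added participants or visits. Gestational age is measured at screening and delivery is tracked. The downside is that visit and birth dates must be recorded, from the interview and the medical records already used for cross-checking. The article does not say that these dates are captured, and home-birth dates may rest on interview or fieldworker tracking alone.

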### Data quality control

In this investigation, mobile-phone-based voice message will be used for reminders of ANC and PNC follow-up appointments and EDD with information about their advantages. This message will be sent in the local language (Oromiffa) and integrated into regular automatic mobile voice messaging at every 2-week interval. The content of the voice messages will be recorded on m-health mobile phones for all who are conducting the study for pregnant mothers under the interventions. Moreover, all enrolled mothers will be oriented as they will receive voice messages regularly from the date of enrollment for appointment reminders.

Data collectors will be given a 5-day intensive training on the contents of data collection tools and data collection procedures. The questionnaire will be prepared in English and translated into the local language for interview purposes and back into the English language for data analysis and to maintain consistency of information. The data will be checked for completeness at all stages of the data collection and possible errors will be returned to the data collectors for correction. Furthermore, a focal person will be assigned to study sites throughout the study period as supervisors and, every 2 weeks, the activities will be audited by the investigators and recorded. Network and electricity challenges will be settled with a systematic way of shifting time of communication without deleting the number of communications. The pre-test will be done on 5% of the total sample size away from the actual study site. Moreover, an independent quality control team will monitor the quality of the treatment or intervention. This team will visit the study process three times (at the start of the intervention, midterm of the intervention and at the end line) until the investigation is completed.

## Discussion

Mobile technology has greatly improved health care service provision at the individual, community and system level. Related with this, few studies focusing on adherence to maternal health care service use have been done in sub-Saharan African (SSA). In previous studies, participants have been selected from health facilities [16, 25–31], whereas the current study will focus on the intervention of mobile-phone-based voice messages for early initiation of maternal health care service use and its uptake. In this investigation, the study subjects will be recruited from the community by using a pregnancy screening test (HCG urine test) and portable U/S to include only those mothers with a GA of less than 16 weeks. This GA is preferred because it is recommended that all pregnant mothers should have their first ANC visit within first 12 weeks of GA, otherwise before 24 weeks.

More specifically, this investigation may uncover concerns regarding poor maternal health care service utilization unique to low-resource settings and will influence m-health program implementation, assuming that this trial demonstrates effectiveness.

There is also limited evidence which shows the effectiveness of m-health on maternal health care service use in low- and middle-income countries. Thus, mobile-phone-based voice message trial study is carefully designed with the assumption of achieving high maternal care service utilization among treatment group as compared to control. In turn, the intervention should reduce adverse pregnancy outcomes.

Randomized controlled trial studies, which were conducted in Zanzibar, Kenya and Nigeria at different times to evaluate the effect of m-health on maternal health care service utilization, have shown a promising outcome on maternal health care service utilization [16, 28, 32, 33]. However, in all aforementioned investigations the study participants were recruited from health facilities which may not show the effect of m-health on early initiation of maternal health care service use. Thus, for the current study, recruitment and enrollment of the study participants will be conducted at the community level. In addition, this investigation will enroll only those mothers at less than 16 weeks of GA to test the effectiveness of m-health on early initiation of maternal health care service use and its uptake. It is also recognized that m-health is a dynamic issue with the fast transfer in both technology and information literacy for developing countries. Hence, there is a need to examine what works or does not work yet and to establish a standard in this area. Therefore, this mobile-phone-based voice message trial study should generate strong evidence on maternal health care service utilization in resource-limited settings with poor literacy, which can be generalizable to similar populations in various settings.

